**Sample size estimates**

Studies comparing ondansetron versus placebo are available in the literature while it was impossible to identify studies comparing ondansetron and domperidone. Two studies evaluating domperidone versus placebo were also identified, even if characterized by low methodological quality and small sample size. Based on the available literature, it appears plausible to hypothesize that ondansetron is more efficacious in comparison to placebo or domperidone and therefore design the study as a superiority trial. For sample size estimation we specifically referred to the Roslund RCT (22) that implemented a similar protocol to ours (enrolment of subjects with clinical acute gastroenteritis who failed initial ORS administration in the ED). Taking into account the above stringent eligibility criteria, we estimate that the enrolment of 540 children (i.e. 180 patients in each arm) will provide the study with a statistical power of 80% to detect a change from 50% in placebo group to 35% in domperidone group and 20% in ondansetron group in the proportion of children requiring nasogastric or intravenous rehydration, given a two-sided type I error of 0,05. Given the lack of available efficacy estimates, domperidone efficacy was estimated as intermediate between ondansetron and placebo.

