**Statistical analysis**

Baseline characteristics of the three groups will be compared by the chi-square test for proportions and the analysis of variance or Kruskal-Wallis test (depending on data distribution) for continuous variables. Relative risks and 95% confidence intervals will be presented for categorical data while means and standard deviations for continuous data. For categorical outcomes, differences between groups will be evaluated using the chi-square test; for continuous outcomes using analysis of variance or Kruskal-Wallis test, depending on data distribution. Analyses will be performed with STATA software (version 9) according to the intention-to-treat principle. All p values will be two-sided, with a p value of less than 0.05 used to indicate statistical significance.

Two interim analysis are planned, following the criteria defined by O'Brien-Fleming (Schulz KF. Lancet 2005;365:1657-61). The first interim analysis is planned at July 2013, two years after the enrolment of the first subject in the study. The interim stopping level (p value) for the difference between ondansetron vs domperidone/placebo is set at 0.0005. The second interim analysis is planned for November 4th 2013 (the official closing date of the study) if: 1) the first analysis had not achieved the necessary significance, or 2) the initially estimated sample size had not been reached. The interim stopping level (p value) for the difference between ondansetron vs domperidone/placebo is set at 0.014.

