**Timing**

A period of 24 months will be required to carry out the study. The recruitment period will last 18 months. Each patient will be recruited at the ED of the participating centres and followed up every 30 minutes at least for 6 hours. Each patient will be contacted by phone 48 hours after ED discharge to evaluate long-term outcomes. Every 6 months research meetings between Coordinating and Participating Units will be arranged to discuss research development and address any emerging issue. The final report will be prepared within the 24 month period.

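### The protocol puts the first two levels of a three-look O'Brien-Fleming design on calendar dates, the second being the closing date, and gives no final level, so the overall error is undetermined

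*Supplement*

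**What the plan says.** All references are to the final protocol in the Supplement.

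- **Statistical analysis, scheme:** "Two interim analysis are planned, following the criteria defined by O'Brien-Fleming".
- **First look:** "The first interim analysis is planned at July 2013, two years after the enrolment of the first subject in the study". Its level: "The interim stopping level (p value) for the difference between ondansetron vs domperidone/placebo is set at 0.0005".
- **Second look:** "The second interim analysis is planned for November 4th 2013 (the official closing date of the study". Its level is 0.014, for the same ondansetron comparison. It is to be done if the first look missed significance or if the planned sample size had not been reached.
- **General level, same section:** "All p values will be two-sided, with a p value of less than 0.05 used to indicate statistical significance". Relative risks are to be given with 95% intervals.
- **Sample size estimates:** 540 children, 180 per arm, which "will provide the study with a statistical power of 80% to detect a change from 50% in placebo group to 35% in domperidone group". The rate assumed with ondansetron is 20%. The level is stated as "given a two-sided type I error of 0,05".
- **Timing:** "The recruitment period will last 18 months", within a 24-month study.

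Neither look is tied to a number of patients or a fraction of the information. No level is given for a third analysis, and nothing says whether recruitment continues after the closing date.

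**The concern.** A group-sequential boundary keeps the overall error at its target only as a complete set: all the looks, at roughly the planned fractions of information, including the last. Here two of three levels are given, and they are attached to dates. The level meant for two thirds of the information falls on the day the study closes, so it may be the last test made.

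If it is the last, most of the 5% is left unused and power is lost. If a later analysis follows, the only other level in the text is 0.05, which takes no account of the interim looks. In either case, a closing-date p value between 0.014 and 0.05 is significant under the general sentence and not under the interim sentence. A 95% interval could also exclude no effect while the 0.014 test fails.

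The condition for the second look adds to this. Because its two parts are joined by 'or', a shortfall in numbers calls for a second look even if the first boundary was crossed. A non-significant first look calls for a test at 0.014 even if all 540 children are in hand.

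**Working it through.** **1. Reproduce the plan's levels.** For three equally spaced looks the O'Brien-Fleming critical values are c_k = C·√(3/k). C is chosen so that 1 − P(|Z_k| < c_k for all k) = 0.05, with Corr(Z_j, Z_k) = √(t_j/t_k). Numerical integration gives C = 2.004.

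| Look | Information | c_k | Two-sided p | Protocol |
|---|---|---|---|---|
| 1 | 1/3 | 3.471 | 0.00052 | 0.0005 |
| 2 | 2/3 | 2.454 | 0.0141 | 0.014 |
| 3 | 1 | 2.004 | 0.0451 | not stated |

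The two stated levels match looks 1 and 2 at the printed precision.

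**2. Reproduce the sample size.** For 50% v 35% at two-sided 0.05 and 80% power, the two-proportion formula gives 170 per arm, or 183 with continuity correction. The stated 180 is consistent with this and was set at the full 0.05.

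**3. Overall error if the closing-date look is the last.** With levels 0.0005 and 0.014 only, the error is 1.42% when look 1 holds half of look 2's information and 1.40% when it holds 95%. The spacing hardly matters.

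**4. Overall error if a later final analysis is made.** Columns 1 and 2 are the assumed share of the final information at each interim look.

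| Look 1 | Look 2 | Final at 0.05 | Final at 0.045 |
|---|---|---|---|
| 0.30 | 0.35 | 5.91% | 5.44% |
| 0.43 | 0.50 | 5.70% | 5.23% |
| 1/3 | 2/3 | 5.45% | 4.99% |
| 0.60 | 0.70 | 5.38% | 4.92% |
| 0.70 | 0.80 | 5.21% | 4.74% |
| 0.80 | 0.90 | 5.06% | 4.57% |
| 0.81 | 0.95 | 5.01% | 4.51% |

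The final level that gives exactly 5% overall is 0.0451 at equal thirds, 0.0477 at 0.70/0.80 and 0.0494 at 0.80/0.90. It depends on the actual spacing, which the dates do not fix.

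**5. Power if closing is the last look.** Power = Φ[(|p1 − p2| − z·s0)/s1], where s0 is the pooled and s1 the unpooled standard error. Ondansetron v domperidone, 20% v 35%:

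- 180 per arm: s0 = √(2 × 0.275 × 0.725/180) = 0.0471; s1 = √((0.35 × 0.65 + 0.20 × 0.80)/180) = 0.0464.
  - At 0.05: (0.15 − 1.960 × 0.0471)/0.0464 = 1.24, power 89%.
  - At 0.014: (0.15 − 2.457 × 0.0471)/0.0464 = 0.74, power 77%.
- 120 per arm (an assumed shortfall): s0 = 0.0576, s1 = 0.0568. Power is 74% at 0.05 and 56% at 0.014.

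Ondansetron v placebo (20% v 50%) at 0.014 keeps more than 99% power at either size.

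**6. What the closing-date look could use.** If 0.0005 was spent at the first look and closing is final, the last level that gives 5.0% overall is 0.0499 when look 1 holds half the information and 0.0500 when it holds 86%. At 0.0499, power for ondansetron v domperidone with 180 per arm is back to 89%.

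**The case against.** The protocol names the O'Brien-Fleming criteria and calls both levels interim. Two interim looks imply a third analysis, and a statistician would supply 0.045 for it. With that level the error is 4.99% at equal spacing. This argument stands against one reading that a reader might draw, that the trial can never run at its stated 5%. The documents do not support that reading: the error is undetermined, and one completion of the scheme delivers 5%. But that level is unwritten, the only written alternative is 0.05, and dates do not secure equal spacing.

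The possible inflation is also small. A reader might take 5.4% or 5.5% as the trial's error rate, but that figure needs both a later test at 0.05 and looks near equal thirds or 60% to 70% of the information. A late second look brings it close to 5.0%. The 1.4% branch is conservative and carries no excess false-positive risk.

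On power, a reader might apply 0.014 to placebo against domperidone (50% v 35%), where the loss would look larger. The interim levels name only the ondansetron comparison, so that contrast should be left out. For ondansetron v domperidone, the shortfall at full size against the stated 80% is 3 points. At 120 per arm, part of the loss comes from the smaller sample itself.

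Finally, the documents give no accrual figures. July to November 2013 is roughly month 24 to month 28, which suggests that the two looks lie close together, but only under assumed even accrual.

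**Conclusion.** Wrong as written. The stated thresholds do not together deliver the stated two-sided 5%, because the set is incomplete and its second member falls on the closing date. Overall error per comparison is 1.4% if closing is the last look. It is about 5.0% to 5.9% if a later analysis uses 0.05, with the second look anywhere from 35% to 95% of the final information. It is about 5% if an unstated 0.045 is used at near-equal spacing.

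The practical cost is greatest in the first case: 77% instead of 89% power for ondansetron v domperidone at 180 per arm, or 56% instead of 74% at an assumed 120. The more immediate problem is that a closing-date p value between 0.014 and 0.05 has no single meaning.

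The error figures are for one comparison. The text does not say whether domperidone and placebo are pooled or compared separately with ondansetron. Power rests on the protocol's own event rates.

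**What to change.** In the interim paragraph of the Statistical analysis section:

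1. State whether the closing-date analysis is final.
2. If it is, and the first look was tested at 0.0005, test it at the remaining alpha, about 0.0499, in place of 0.014.
3. If recruitment continues to 540, replace 0.05 at the final look with a level computed from the numbers actually randomised at each look. It equals 0.045 only if the looks fall at equal thirds.
4. Match the coverage of the reported intervals to the level used.
5. Change 'or' to 'and' in the condition for the second look.

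Items 2 and 3 are alternatives; the answer to item 1 decides which applies. The Timing section should then agree with that answer. The cost is a few sentences of protocol wording, with no additional patients or data. The choice should be recorded before any comparison by arm is seen.

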**Drugs production and supply**

Drugs manufacture will be committed by the Coordinating Centre to Monteresearch S.r.l. ([name]), a pharmaceutical laboratory licensed by the Italian Medicines Agency (AIFA) to produce and manage medical products for clinical trials according to Good Manufacture Practice. All the manufacturing operations will be developed and agreed with the Clinical Trial Service and Clinical Trial Quality Team of the Coordinating Centre. Monteresearch will dispense active drugs and placebo directly to each participating centre.

**Feasibility**

The Institute for Maternal and Child Health Burlo Garofolo is an IRCCS with a wide experience in carrying out clinical trails. In the Osservatorio Nazionale sulla Sperimentazione Clinica dei Medicinali (OsSC AIFA), 14 clinical trials carried out and coordinated by the Institute are recorded. Among those, two trials took place in EDs and one was funded by AIFA in the independent research grant 2006 (Randomized Controlled Double-Blind Vs. Placebo Multicentre Study On The Safety And Effectiveness Of Thalidomide In The Treatment Of Refractory Crohn’s Disease And Ulcerative Colitis In Children And Adolescents, Cod.: FARM64J2EB).

A Clinical Trial Quality Team (CTQT) has been established to guarantee a high quality of no profit clinical trials funded by the Institute. The CTQT establishment was notified to AIFA (Uffici Promozione e Ispezioni Good Clinical Practice) and the Institute has been included in the AIFA network for no profit clinical trial quality (“Rete delle strutture partecipanti al Progetto AIFA per la qualità nelle sperimentazioni no profit”).

A multidisciplinary (clinicians and epidemiologists) steering committee will establish to monitor the data, to ensure patient safety and to act as reference for Participants Units. Any problem arising during the trial will be discussed by committee members and decision will be shared with Participants Unit. The committee will be constituted by researchers who are either not directly involved in actual field work (dr. [name], dr. [name]) or are external to the study (dr. [name], epidemiologist, dr. [name], paediatric gastroenterologist).

**Timing**

A period of 24 months will be required to carry out the study. The recruitment period will last 18 months. Each patient will be recruited at the ED of the participating centres and followed up every 30 minutes at least for 6 hours. Each patient will be contacted by phone 48 hours after ED discharge to evaluate long-term outcomes. Every 6 months research meetings between Coordinating and Participating Units will be arranged to discuss research development and address any emerging issue. The final report will be prepared within the 24 month period.

**Good clinical practices**

The steering committee will monitor the safety and the overall quality and scientific integrity of the study. Every 6-8 months a monitor visits will be carried out in each centres by members of the steering committee.

**Opening of the blind**

The opening of the blind will be allowed in the presence of one of the following criteria:

1. appearance of a serious, unexpected adverse event;

2. need to administered a antiemetic drug for significant worsening of vomiting.

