**The need for further evidence and potential transferability to clinical practice**

The above reported evidence shows the efficacy of the most recently registered molecule (ondansetron), but the studies were carried out on very heterogeneous populations for which risks, costs and benefits were not sufficiently assessed. The same evidence showed that a proper evaluation of anti-emetics drugs largely used in clinical practice (13), such as domperidone, is completely lacking. This lack of knowledge about antiemetics is particularly important considering the restricted indications for their use in Italy (this is particularly true for metoclopramide). In fact, these agents’ potential side effects as extra-pyramidal manifestations, lack of consciousness, convulsions are mostly dose-dependent and they have been addressed by a recent ad hoc report by AIFA paediatric commission (17).

In light of the above considerations, we propose a multicentre study comparing the efficacy of ondansetron and domperidone for the symptomatic treatment of vomiting in acute gastroenteritis. The study aims at answering the following clinical questions: a) would anti-emetics agents reduce the percentage of children who keep vomiting? b) would anti-emetics treatment favour the oral rehydration and reduce the need for nasogastric or intravenous fluid rehydration? c) would the treatment reduce the percentage of children accessing health services and needing hospital admission?

We believe that the results of such a trial could significantly impact current clinical practice. In fact it would define the real efficacy of domperidone largely used in clinical practice (despite the lack of a clear evidence-based assessment and a controversial safeness profile) compared to ondansetron whose use to treat vomiting in AG is not yet authorized in Italy despite evidence supporting its possible use. The design of this RCT, which closely reflect current clinical practice in EDs, should allow immediate transferability of results.

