**Annex 1. Definitions**

**Clinical diagnosis of acute gastroenteritis**

We refer to the NICE guideline ([www.nice.org.uk/guidance/index.jsp?action=download&o=42316](http://www.nice.org.uk/guidance/index.jsp?action=download&o=42316)) that recommends:

"When considering a diagnosis of gastroenteritis, look for the following key characteristics:

- a recent change in stool consistency to loose or watery stools;
- recent onset of vomiting;
- recent contact with an individual with acute diarrhoea;
- exposure to known source of enteric infection (water or food borne);
- recent foreign travel.

Consider the following symptoms and signs as possible indicators of diagnoses other than gastroenteritis:

- high fever:

- age less than 3 months: > 38 °C

- age more than 3 months: > 39 °C.

- rapid breathing or laboured respirations
- altered conscious level (irritability, drowsiness)
- photophobia, neck stiffness and/or bulging fontanelle (in infants)
- non-blanching (haemorrhagic) rash
- blood and/or mucous in stool
- bilious vomiting (green)
- severe or localised abdominal pain
- abdominal distension or rebound tenderness."

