**Study Population**

The study will be conducted in hospital and the recruitment setting will be the paediatric emergency departments (ED). Children between 1 to 6 years will be included in the study.

Consecutive subjects accessing the ED during a 18 months period will be evaluated for inclusion/exclusion criteria by the doctor on call. The following inclusion and exclusion criteria will be used:

Inclusion Criteria

1) age from 1 to 6 years;

2) presumptive clinical diagnosis of acute gastroenteritis in patients with vomiting, with or without diarrhoea (see Annex 1 for AG clinical diagnosis and vomiting definitions);

3) more than three episodes of non-bilious, non-bloody vomiting within the previous 24 hours;

Exclusion Criteria:

1) treatment with antiemetics or antidiarrhoic drugs in the 6 hours prior to access to ED;

2) underlying chronic diseases (eg, malignancy, gastroesophageal reflux, migraine, renal failure, hypoalbuminemia, liver disease);

3) severe dehydration defined by a standard clinical score of >18 for children 12-24 months or >16 for children >24 months of age (see Annex 1) (20);

4) known hypersensitivity to ondansetron or domperidone;

5) previous enrolment in the study

6) concomitant use of drugs that prolong the QT interval (i.e., macrolides, quinolones, ketoconazole, fluconazole, salmeterol, trimetoprim)

7) language barriers or inability to perform the telephone follow-up

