**Blinding**

The pharmaceutical preparation will be directly sent to participating centres in closed, opaque and consecutive numbered bags by the central pharmacy. Drug preparations will be indistinguishable by taste, odour and appearance. All study investigators, personnel, and participants will be blind to preparations administered.

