| **Methods section.**  A paragraph on the opening of the blind was added:  **"Opening of the blind**  The opening of the blind will be allowed in the presence of one of the following criteria:  1. appearance of a serious, unexpected adverse event;  2. need to administered a antiemetic drug for significant worsening of vomiting." | 02.05.2011 |

* All changes were submitted and approved by the Ethic Committee of all the participating centers.

1. Published on BMC Pediatrics:

   [name] et al. Oral ondansetron versus domperidone for symptomatic treatment of vomiting during acute gastroenteritis in children: multicentre randomized controlled trial. BMC Pediatr 2011;11:15. [↑](#footnote-ref-2)
2. This standard protocol is the result of the combination of international guidelines recommendations and study committee consensus derived from ED clinical practice. [↑](#footnote-ref-3)

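### The written grounds for opening the blind leave out a serious reaction classed as expected, even when knowing the arm would help the doctor treat or diagnose the child

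*Supplement*

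**What the plan says.** The final protocol, Methods, Opening of the blind, gives two alternative grounds:

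- "appearance of a serious, unexpected adverse event";
- "need to administered a antiemetic drug for significant worsening of vomiting".

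The Summary of changes repeats the same two. No other section shown offers a further route, such as a medical-emergency clause or investigator discretion.

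Four other places bear on the point.

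- **Blinding:** "All study investigators, personnel, and participants will be blind to preparations administered". The treating doctor therefore does not know the arm.
- **Background, on the need for further evidence** (carried unchanged into the final protocol): for antiemetics as a group, "potential side effects as extra-pyramidal manifestations, lack of consciousness, convulsions are mostly dose-dependent". The same section describes domperidone's safety as controversial.
- **Study Population, exclusion criterion 6:** bars "concomitant use of drugs that prolong the QT interval". No reason is stated.
- **Annex 1, clinical diagnosis of acute gastroenteritis:** lists "altered conscious level (irritability, drowsiness") among the signs that may point to a different diagnosis.

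**The concern.** The first ground has two conditions joined together: the event must be serious and it must be unexpected. In safety reporting, *unexpected* usually separates events already known for a product from those that are not. Read that way, a serious reaction that the authors anticipated fails the first ground. Unless vomiting has also worsened enough to need an antiemetic, it fails the second as well.

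Expectedness is a sensible filter for reporting. It is a poor one for emergency unblinding, where the question is whether knowing the allocation would change what is done for the child. Suppose a child becomes drowsy or convulses after dosing. The doctor must weigh a drug reaction against another illness, and Annex 1 already treats altered consciousness as a reason to look beyond gastroenteritis. One arm in three is placebo. Learning that the child had placebo would rule out a study-drug reaction and direct attention to the other diagnosis.

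What is at stake is the care of a small number of individual children. Sample size, type I error and the efficacy comparison are not affected.

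**Working it through.** The core of the check is textual. The plan gives no figure on this point to reproduce.

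**Step 1. Test a serious reaction of a kind named in the Background against each ground.**

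| Event | Ground 1 (serious and unexpected) | Ground 2 (antiemetic needed) |
|---|---|---|
| Serious, classed as unexpected | met | not needed |
| Serious, classed as expected, vomiting not worse | not met | not met |
| Serious, classed as expected, vomiting clearly worse and antiemetic needed | not met | met |

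The gap is the second row. Whether a real event falls there depends on how *unexpected* is read. The text shown neither defines the word nor lists expected events.

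**Step 2. How many children might this concern?** The documents give no rate of serious known reactions, so I assume a range of 0.1% to 2% per child.

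Input: 180 children per arm (Sample size estimates), so two active arms give n = 2 × 180 = 360.

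Expected number = n × r:

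- r = 0.1%: 360 × 0.001 = 0.36
- r = 0.5%: 360 × 0.005 = 1.8
- r = 1%: 360 × 0.01 = 3.6
- r = 2%: 360 × 0.02 = 7.2

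These figures count every serious known reaction. The cases that matter are those where knowing the arm would change diagnosis or treatment, which is an unknown and possibly small fraction. The range of about 0.4 to 7 is therefore an upper bound at each assumed rate. The low end is more plausible: the child receives one weight-based dose, repeated only after vomiting within 15 minutes (Intervention), and the Background calls these effects mostly dose-dependent.

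**Step 3. How many extra openings could a wider rule cause?** The decision to open is made before the arm is known, so serious events on placebo count too. Take the same assumed rate in all n = 540 children, and suppose every such event led to opening. The upper limit is the exact binomial 97.5th percentile.

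| Assumed rate | Expected, 540 × r | 97.5th percentile | Share of 540 |
|---|---|---|---|
| 0.1% | 0.54 | 2 | 0.4% |
| 0.5% | 2.7 | 6 | 1.1% |
| 1% | 5.4 | 10 | 1.9% |
| 2% | 10.8 | 18 | 3.3% |

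This too is a ceiling, since the proposed wording opens the blind only where the allocation is needed.

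**The case against.** The strongest objection is that nothing shown makes these reactions *expected* for the two study drugs. The Background's section on antiemetic agents ties dystonic reactions to phenothiazines and metoclopramide, neither of which is given here. The list of side effects quoted above is about antiemetics in general and directly follows a remark about metoclopramide. For ondansetron, the Background reports no significant difference from placebo in side effects apart from more diarrhoea. A doctor could reasonably call a convulsion after one dose unexpected, and the first ground would then apply. This stands, and it makes the point conditional. It does not remove it: with the term undefined, centres in a multicentre trial can reach different answers.

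Second, the rule is permissive. A reader might infer that opening is forbidden in every other case. The text does not say so, because it states when opening is allowed and does not contain the word *only*. What can be said is that a doctor acting outside the two grounds would have no written ground to rely on.

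Third, a reader might infer that the plan leaves out reactions whose treatment differs between ondansetron and domperidone. The documents describe different receptor actions for the two drugs but identify no reaction with arm-specific treatment. The supportable argument is the diagnostic one, active drug against placebo, and even that is clinical reasoning. The list in Annex 1 was written for making the initial diagnosis and not for events after dosing.

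Fourth, exclusion criterion 6 might be read as proof that rhythm effects were foreseen. It suggests as much, but the protocol gives no reason for it.

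Finally, one could turn the assumed rates into a high probability of at least one affected child. At 0.5% and above that probability exceeds 80% (1 − 0.995^360 = 0.84). This would overstate the case, because the rates have no anchor in the documents and count reactions for which the arm may not matter.

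**Conclusion.** The point holds as a conditional gap in the safety wording. The two written grounds do not cover a serious adverse event classed as expected, and no general medical-need ground appears in the text shown. It rests on one assumption, that a centre classes the antiemetic reactions named in the Background as expected. If it classes them as unexpected, the first ground applies and the gap closes.

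The size is small and uncertain: at most about 0.4 to 7 of 360 actively treated children at assumed rates of 0.1% to 2%, with the low end more plausible and only some of these needing the allocation. No bias in the efficacy comparison follows from the gap. It is worth correcting because the correction is cheap and removes a doubt that a doctor should not have to resolve in an emergency.

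**What to change.** Reword the first criterion as: *any serious unexpected adverse event, or any serious adverse event, expected or not, when knowing the drug given is needed for the child's diagnosis or treatment*. Leave the second criterion as it is.

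The cost is one sentence, submitted as an amendment by the route already used: "All changes were submitted and approved by the Ethic Committee of all the participating centers".

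The downside is a few more openings of the blind, some possibly before the decision on nasogastric or intravenous rehydration, so that staff would know the arm when the primary outcome is decided. Under the assumptions above, the upper limit is 2 to 18 of 540 children (0.4% to 3.3%).

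No new sentence on analysis is needed. Statistical analysis already states: "Analyses will be performed with STATA software (version 9) according to the intention-to-treat principle". Children whose allocation is opened therefore remain in their randomised arm.
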